#### Fidelity of treatment

Each therapist will be trained by HT and assessed in vivo at interviews with patients using an adaptation of the Cognitive Therapy Rating Scale (CTRS), a necessary change for a population that largely regards its anxiety as an appropriate mood to monitor health [20]. Supervision in vivo will continue until at least a 75 % of maximum score is achieved.

### Status of the trial

Recruitment to the study began in July 2012 and the last patient was recruited in January 2015. No data have currently been examined. The CONSORT diagram illustrates the high numbers of people who present with potential non-cardiac chest pain (Fig. 1). 68 patients were recruited, a lower level than planned, but the revision in the clinically important difference (see above) makes the study only slightly underpowered.

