### Target number of participants

From previous work with the Health Anxiety Inventory we calculated that a difference between the scores of 4 points is a clinically significant difference (but this is currently being reassessed as 2 may be a more appropriate value). Using data from a similar randomised controlled trial [17] we demonstrated a significant benefit between CBT and control with a sample of 49 patients. In this study with a standard deviation for the change of HAI at 1 year as 6.0 a sample size of 96 patients would be have 90 % power to demonstrate significance at the two-sided 5 % significance level. However, it is expected that a current very similar project in New Zealand under the supervision of RM, with HT as an applicant, will provide very similar data from at least a subset of their sample that will allow some form of combination of data, such as individual meta-analysis, that will add to the power of the study.

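### Lowering the important difference from 4 to 2 points makes the shortfall at 68 patients much worse, not slight: power for 2 points is about 27%

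*Protocol article*

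**What the plan says.** Under Target number of participants, the article takes it that "a difference between the scores of 4 points is a clinically significant difference" and adds in brackets "but this is currently being reassessed as 2 may be a more appropriate value". With a "standard deviation for the change of HAI at 1 year as 6.0", it states that "a sample size of 96 patients would be have 90 % power" at the two-sided 5% level. The same section expects that some combination with a parallel New Zealand trial will add power.

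Under Status of the trial, the article reports that recruitment closed in January 2015 with 68 patients, below plan, and that no data had been examined. It then says that "the revision in the clinically important difference (see above) makes the study only slightly underpowered". The cross-reference can only be to the bracketed remark about 2 points, because no other revision of the important difference is described.

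Under Analyses, the primary comparison is of mean change in the Health Anxiety Inventory from baseline to 6 months. A random effects model with baseline adjustment is to estimate and test the differences at 6 and 12 months.

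**The concern.** A smaller target difference is harder to detect and needs more patients. The article offers the move from 4 to 2 points as the reason why a recruitment shortfall matters little, when that move enlarges the shortfall.

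The sentence guides how the result will be read. If the trial is taken to be nearly adequately powered for 2 points, a non-significant result will look like reasonable evidence that CBT-CP has no important effect. On the article's own figures, COPIC alone would miss roughly three in four true effects of that size. The important difference is also left open between 2 and 4 points after recruitment has closed, so the yardstick for clinical importance is not settled.

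**Working it through.** **Inputs.** From Target number of participants: difference 4 points (possibly 2), SD of change 6.0, power 90%, two-sided 5%, total 96. From Methods/design: equal allocation. From Status of the trial: 68 recruited. Two assumptions are added: 34 per arm (arm counts are not given in the text), and the 1-year SD applied to the 6-month primary outcome.

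**1. Reproduce the planned size.** Per arm, n = 2(1.96 + 1.2816)² × SD² / difference².

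- Difference 4: 2 × 10.507 × 36 / 16 = 47.3, so 48 per arm and 96 in total. This matches the article. Exact t-test power at 48 per arm is 89.8%.

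**2. Required size for 2 points.**

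- 90% power: 2 × 10.507 × 36 / 4 = 189.1, so 190 per arm and 380 in total.
- 80% power: 2(1.96 + 0.8416)² × 36 / 4 = 141.3, so 142 per arm and 284 in total.

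Halving the difference multiplies the requirement by four, apart from rounding.

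**3. Power with 68 patients.** The standard error of the difference is 6.0 × √(2/34) = 1.455. The noncentrality is 4 / 1.455 = 2.75 for 4 points and 2 / 1.455 = 1.37 for 2 points. Two-sided 5% t-test, no loss:

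| Patients | 4 points | 2 points |
|---|---|---|
| 96 (planned) | 90% | 37% |
| 68 (recruited) | 77% | 27% |

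The normal approximation gives 78.5% and 27.9% for the 68. Even the full planned sample would have been far too small for 2 points.

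**4. What 68 patients can detect.** About 4.1 points with 80% power and 4.8 points with 90% (4.7 by the normal approximation). For 90% power at 2 points the SD of change would have to be about 2.5 rather than 6.0.

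**5. Can anything in the plan rescue the sentence?**

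- *Baseline adjustment.* If 6.0 is the SD of change, and the SDs at baseline and follow-up are equal, adjustment multiplies the variance by (1 + r)/2, where r is the baseline to follow-up correlation. The article gives no r. For an assumed r of 0.3 the SD becomes 6.0 × √0.65 = 4.84, and for 0.7 it becomes 6.0 × √0.85 = 5.53. Power for 2 points is then about 39% and 31% respectively; for 4 points it is about 92% and 84%.
- *Pooling with New Zealand.* Adding all 126 patients gives 194, or 97 per arm. With the same SD assumed, power for 2 points is about 64%.

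**6. What the confidence interval could show.** With 34 per arm and SD 6.0, the 95% half-width is 1.997 × 1.455 = 2.9 points.

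**The case against.** The strongest reply is that 27% belongs to one simple calculation. The article also plans a baseline-adjusted model, which would raise power. The SD is a 1-year value, while the primary outcome is at 6 months. The New Zealand data are expected to add power. The move to 2 points is described as tentative, no data had been examined, and an analysis plan that is not shown may settle the value. The error is one sentence in a status section and changes no endpoint, analysis or patient procedure.

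Much of this stands as a limit on precision. The figures need their assumptions beside them, and 77% may understate the power for 4 points. None of it reverses the direction. Adjustment leaves power for 2 points below 40% over the assumed range. Pooling the whole New Zealand sample still gives only about 64%, the form of combination was undecided and might cover only a subset, and the sentence at issue does not rely on pooling. A tentative revision cannot serve as the reason why the shortfall is slight.

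Three stronger readings are tempting and are not supported:

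- A reader might infer that a non-significant result could never exclude a 2-point benefit. With a half-width of about 2.9 points, an estimate more than about 0.9 points in favour of control would exclude it.
- A reader might infer that the article expects missing data and failed to allow for it. The Analyses section plans to examine the missing-data mechanism but predicts no rate, and an attrition allowance is detail that a condensed article may leave out.
- A reader might infer that the important difference will be chosen to suit the result. The article shows only that it was unsettled, and says that no data had been looked at.

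**Conclusion.** Wrong as written. The planned size of 96 reproduces from 4 points and SD 6.0, so the inputs are those that the article used. On the same inputs, moving to 2 points raises the requirement to about 380 analysed patients for 90% power, against 68 recruited. Power at 68 is about 77% for 4 points and about 27% for 2 points, assuming 34 per arm, the 1-year SD at 6 months, an unadjusted two-sided 5% t-test, no loss, and COPIC alone. A description as slightly underpowered could be defended only for the 4-point difference, which is the opposite of the reason given.

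**What to change.** Replace the sentence under Status of the trial with wording such as: *With 68 patients randomised (34 per arm assumed), an SD of change of 6.0 taken from 1-year data, an unadjusted two-sided 5% t-test and no loss to follow-up, power is about 77% for a 4-point difference and about 27% for a 2-point difference. A 2-point target would need about 380 analysed patients for 90% power, so the revision increases the shortfall.* If the adjusted or pooled figures are added, give the assumed correlation and SD with them.

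Fix the important difference at 2 or 4 points, with its source, before outcome data are opened. Interpret the 6-month estimate and its 95% confidence interval against that value, and do not treat non-significance alone as evidence that there is no important effect.

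The cost is wording only: no further recruitment and no change of design, but a less favourable statement of power.

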**Fig. 1 Fig1:**
[figure not shown]
COPIC Trial Profile

## Discussion

The trial has been a difficult one to undertake because of the several ways in which non-cardiac chest pain is assessed in general. It has also highlighted a lack of close liaison between accident and emergency and cardiology departments, and surprise among many cardiologists that so many patients with non-cardiac chest pain are seen and discharged by accident and emergency staff without ever seeing a specialist in cardiology. There was also some evidence that dogmatic reluctance to follow any other route different from the standard investigation pathway sometimes hinders acceptance of a likely psychological explanation for symptoms. This is also reflected in the relatively high proportion of patients who refused randomisation (37 %) after passing through all other part of the assessment process. This reluctance to take part in psychological interventions has been noted by others in this field [6] and will probably only be overcome by increasing mental health literacy in both patients and hospital staff.
